## Formative phase

The ReHAB intervention includes two core components: (1) community education and awareness and (2) structural heat adaptation modifications (figure 1). The formative phase comprised the following activities, which were undertaken to identify the specifics of the potential interventions which are plausible, acceptable and cost-effective.

### Systematic review

We conducted a systematic review of existing community-based interventions for heat adaptation in LMICs,^27^ analysing 185 studies and identifying effective strategies and highlighting gaps in adaptation strategies. Based on this information, we compiled a list of proven interventions to discuss with local communities and other stakeholders and policymakers.

### Qualitative study

The second part of this formative phase was in-depth interviews and focus group discussions with key stakeholders, including policymakers, relevant government officials at the national/provincial/local administrative level, civil society representatives, and community members, especially women, and the findings of this helped assess the possible education and structural interventions and their mode of delivery. The details of which would be published as a separate paper.

### Consultative workshops

A series of consultation meetings with key stakeholders, ranging from municipal authorities and related government departments and technical experts to community representatives, were held to finalise the intervention plans.

### Site selection

To identify the most feasible and representative location, a comprehensive site selection activity was undertaken across Karachi. A total of 30 potential sites were visited, with multiple visits conducted at each location. These visits involved assessing the built environment, understanding the local socio-economic dynamics, identifying climate-related vulnerabilities and gauging community willingness. Informal discussions were held at each site to capture local perspectives and ensure contextual relevance in site selection.

### Pilot study

A pilot study will be carried out in Karachi involving 80 households to assess implementation and recruitment feasibility, including participant recruitment and retention, acceptability of intervention delivery, adherence to wearable devices, and completeness of data collection procedures. Over the course of this pilot, the full suite of interventions will be delivered, community engagement activities will be implemented, and environmental data will be collected to assess their impact on indoor and outdoor temperatures; details will be published as separate papers. Once the pilot is concluded, the data will be analysed and reviewed in consultation with stakeholders and subject-matter experts. Findings from the pilot will inform refinement of intervention components and study implementation procedures and will not be included in the final trial analysis

## Intervention

### Intervention arm: Resilience and heat adaptation bundle

ReHAB was finalised based on the activities from the formative phase. The ReHAB consists of two components: community education and awareness and participatory structural modifications, which would provide local heat adaptation solutions. Behavioural and educational interventions will be delivered through community mobilisation whereas structural interventions will encompass modifications in the existing structures that communities live in to lower the indoor ambient temperature. Details of each component are provided below:

#### Community education and awareness

This component of the ReHAB will involve community mobilisation, which will include education and awareness activities throughout the intervention duration. Community groups (CGs) will be established in all the 11 intervention clusters with separate male and female representatives working as volunteers. The CGs will be responsible for community mobilisation activities and surveillance for the primary outcome (heat illness). Each CG will comprise 6–8 members, representing a diverse group of people, including local government members, local elders, religious leaders and prominent male and female members of the community. These CGs will facilitate dissemination of early warnings regarding heat waves, awareness sessions and door-to-door outreach focused on heat-health fundamentals, hydration practices, appropriate clothing and daily activity scheduling. CGs will also maintain simple logbooks to track any visit to a healthcare facility within their catchment area.

Also building on this CG platform, hands-on demonstration and reinforcement of specific cooling behaviours will be emphasised. CG members, along with the study team, will lead small-group demos on practical techniques, such as setting up shade cloths, using light-coloured clothing, wet-towel wraps, misting fans, changing work timings and following work-rest-shade cycles to reduce heat exposure. CGs will also distribute the relevant information, education and communication (IEC) material. This structured, behaviour-focused delivery aims to ensure both the uptake and sustainability of protective cooling practices. Community hydration arrangements, like setting up temporary drinking water facilities (‘Sabeels’), will also be put in place as part of the intervention package to reduce dehydration among outdoor workers.

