##### Information, education and communication materials

Findings from the formative phase will guide the development of educational materials. We will develop the following materials.

Posters.Pictorial brochures/flip charts.Short video messages in the local languages (Sindhi, Pashto and Urdu).

IEC materials will be distributed during CG meetings and during follow-ups through data collectors, and short videos will be shared through WhatsApp groups with disappearing message settings turned on (messages that disappear after a single view) to prevent videos from passing on and possibly resulting in control group contamination.

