##### Training

All CGs will be trained in specific awareness and educational messages regarding heat prevention and adaptation measures to assist them in carrying out the sessions. Along with this, all CGs will be trained in the care of temperature devices, Android devices and data loggers and establishing a network within the community for effective surveillance of heat-related illness and hospital visits. The CGs will also be trained to effectively communicate with the community about structural intervention decisions and explain the reason for selecting a particular intervention for a structure.

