### Control arm

The control arm of the study will not receive any intervention other than routine care and information available through existing government response systems, including health and disaster management agencies.

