Data on the signs and symptoms of heat-related illness will be collected through multiple points to ensure no event is missed during the study period. Data collectors will conduct weekly household visits to collect symptom data. Events identified through community surveillance will trigger a household visit by data collectors who will use the same survey tool, and reported health facility visits will be verified through facility records where feasible. Symptoms will be classified as International Classification of Disease-11 and institutional classification of heat illness (figure 2). Data for quality of life will be acquired through multiple surveys of all households included and the respondent for these surveys will be the selected index adult (table 3).

Additionally, at endline, 5 mL of venous blood samples will be collected by trained phlebotomists using standard aseptic techniques from control and intervention households during peak heat in year two of the project. These samples will be stored for further evaluation in our biobank following standard storage guidelines. They may be used to detect heat-related biomarkers in any future research.

Quantitative data collection will be conducted using handheld devices equipped with a customised application developed in Java, using MySQL and SQLite for data storage. The programme will incorporate range and consistency checks, along with skip patterns to reduce data entry errors. Any detected inconsistencies will be addressed by contacting data collectors for verification and correction. Each participant will be assigned a unique code generated by the Android application to ensure anonymity. All data will be securely stored behind firewalls and fully anonymised before analysis.

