### Data collection from subset population

Monthly data will be collected for in-depth understanding of heat stress and intervention effectiveness within the subset population (table 3). This will include thermal comfort, mental health and heat exposure assessment.

**Table 3 T3:** Schedule of outcome assessments and follow-up activities

Parameter	Time points	Details	Devices/Tools	Population/Unit
Primary outcomes				
All heat-related illness	Weekly during peak summers	Heat-related illnesses	Weekly community survey, health facility data, community surveillance	All members of included households
Quality of life	Mid of April, July and December for two consecutive years	Quality of life mean score	WHOQOL-BREF* questionnaire	Indexed adults of all included households
Secondary outcomes				
All-cause mortality	Weekly during peak summers	Any mortality occurring within the included clusters	Weekly community survey, health facility data, community surveillance	All members of included households
Hospital visit/hospitalisation	Weekly during peak summers	Any hospital admission or hospital visit occurring within the included clusters	Weekly community survey, health facility data, community surveillance	All members of included households
Indoor heat index	Continuous throughout the year	Indoor data loggers	iButton, Kestrel Drop D2, Temp-U	All included households
Thermal comfort (home)	Monthly	Self-reported comfort levels	Thermal comfort survey adapted from CHEQ-5†	Indexed adults randomised for sub-group
UTCI§	Continuous throughout summers	Outdoor only	Kestrel Drop D2, Kestrel 5400, HOBO weather station	Overall catchment area
Outcomes measured for subset of population				
Personalised heat exposure	Baseline, monthly	Occupation, sun exposure, illness history, daily routine	Structured survey tool (adapted from HotHaps)‡ and Temp-U	Indexed adults randomised for sub-group
Physiological strain markers	Continuous throughout summers	Heart rate, sleep cycles, VO₂¶ max	Fitbit Inspire 3	Indexed adults randomised for sub-group

* WHOQOL-BREF: World Health Organization Quality of Life - Brief

† Cold and Heat Exposure Questionnaire

‡ High Occupational Temperature Health and Productivity Suppression

§ Universal Thermal Climate Index

¶ Volume of Oxygen

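### Heat-illness and hospital-visit surveillance is given to community groups described only for the intervention clusters, so the arm comparison can mix effect with detection

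*Protocol article*

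**What the plan says.** All references are to the protocol article.

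- **Who the CGs are.** Community education and awareness: "Community groups (CGs) will be established in all the 11 intervention clusters with separate male and female representatives working as volunteers". They deliver the behavioural component (awareness sessions, outreach, demonstrations, early warnings).
- **Their outcome role.** Same section: "The CGs will be responsible for community mobilisation activities and surveillance for the primary outcome (heat illness". It adds: "CGs will also maintain simple logbooks to track any visit to a healthcare facility within their catchment area". The Training section has them "establishing a network within the community for effective surveillance of heat-related illness and hospital visits".
- **How reports enter the data.** Household data collection: "Events identified through community surveillance will trigger a household visit by data collectors who will use the same survey tool". Facility visits that are reported are checked against records where feasible.
- **Sources by outcome.** Table 3 gives the same source list for heat illness, mortality and hospital visits, "Weekly community survey, health facility data, community surveillance", for all members of included households and with no split by arm.
- **Control arm.** "The control arm of the study will not receive any intervention other than routine care" and information from existing government systems. No CG or substitute surveillance is mentioned.
- **Analysis.** Primary outcome analysis uses episodes over person-weeks in a Poisson model with cluster random intercepts. Duplicates across sources are removed; no source is excluded.
- **Education at follow-up.** Information, education and communication materials: "IEC materials will be distributed during CG meetings and during follow-ups through data collectors".

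**The concern.** A rate ratio compares arms fairly only if an event of a given kind is equally likely to be found in each. Here one detection channel is assigned to volunteers who, on the text, exist in one arm only and who also deliver the intervention being tested. An event that only they notice can enter the intervention numerator, while its counterpart in a control cluster may go unrecorded.

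The heat-illness test is also the gatekeeper. Under the fixed-sequence procedure in the Sample size section, quality of life is tested only if heat illness is significant. A distorted first test therefore also decides whether the second co-primary outcome is tested at all.

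Mixed models, robust variances and blinded analysis do not address this, because the distortion lies in the counts themselves.

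**Working it through.** **1. Trace an event through the text.**

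| Step | Intervention cluster | Control cluster |
|---|---|---|
| Weekly data-collector visit | yes | yes |
| Facility-record check of reported visits | where feasible | where feasible |
| CG surveillance and logbook | yes | none described |
| Extra visit after a community report | yes | no stated trigger, unless Table 3 means another channel |
| Counted after de-duplication | yes | yes |

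De-duplication stops double counting. It does nothing about an event found by one source in one arm and by no source in the other. Such events are plausible: the outcome includes heat rash, cramps and fatigue, a new episode can begin after two symptom-free days, and the protocol adds sources precisely so that none is missed.

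**2. Reproduce the planned size.** Inputs from the Sample size section: control proportion 0.289, 30% relative reduction (0.289 × 0.70 = 0.2023), ICC 0.0122, 11 clusters per arm, two-sided 5%, 80% power, 10% attrition.

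- Individually randomised n per arm (pooled-variance formula): 386; with continuity correction, 409.
- Design effect: 1 + (m − 1) × 0.0122. Solving 11m = n × design effect gives m = n(1 − 0.0122)/(11 − 0.0122n).
- n = 386: m = 60.6, and 60.6/0.9 = 67.3. n = 409: m = 67.2, and 67.2/0.9 = 74.7.

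The second result lies within the stated 70–80 households, so the planned size reproduces and is not in question.

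**3. Illustrate unequal detection.** The documents give no capture rates, so r, the ratio of intervention to control ascertainment, is assumed.

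- Observed ratio = true ratio × r.
- Analysed per cluster: 75 × 0.9 = 67.5. Design effect: 1 + 66.5 × 0.0122 = 1.811. Effective n per arm: 11 × 67.5/1.811 = 409.9.
- Power = Φ(d/SE − 1.96), with d = p0 − p1 and SE = √{[p0(1 − p0) + p1(1 − p1)]/409.9}.

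| Assumed r | Observed ratio | p1 | d | SE | Power |
|---|---|---|---|---|---|
| 1.00 | 0.70 | 0.2023 | 0.0867 | 0.0299 | 82.6% |
| 1.10 | 0.77 | 0.2225 | 0.0665 | 0.0304 | 59.0% |
| 1.20 | 0.84 | 0.2428 | 0.0462 | 0.0308 | 32.3% |

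With 63 per cluster (70 × 0.9) and the pooled-variance version, the three powers are 81%, 57% and 31%. An r of 1/0.70 = 1.43 would cancel the planned effect; that is a break-even point, not an expected value.

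**4. Direction.** An extra channel in one arm can by itself only add events there, moving the ratio towards or above 1. The opposite is possible if unblinded volunteers discourage reporting, or if control clusters have a different and more complete channel that the article does not describe. For example, r = 0.90 would turn 0.70 into 0.63.

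**The case against.** The strongest reply is that the main channel is common to both arms. Follow-up surveys run in all 22 clusters, and data collectors visit households weekly. A community report is not itself an outcome: it prompts a data-collector visit with the same tool. Only events that a CG flags and the weekly visit would miss can differ, and these may be few. This stands as a limit on size. It does not restore equality, because the tool is the same but the number of visits is not.

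A second reply is that the article never says control clusters lack community surveillance. Table 3 lists it for all included households, the Control arm section rules out intervention rather than data collection, and a full protocol could describe a control-arm arrangement. This also stands: the absence is inferred. But the article positively assigns the task to groups it places only in intervention clusters, so the passages conflict until reconciled.

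Three stronger readings are tempting and not supported:

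- **Deaths are found more readily in the intervention arm.** CG duties name heat illness and facility visits only. Deaths come in only through the shared source list in Table 3, and weekly visits should find most deaths in either arm.
- **Education is handed out at the visits where outcomes are recorded.** The text says follow-ups, and the article describes both monthly and weekly follow-up. It does not identify which.
- **The power losses are forecasts.** They rest on assumed excesses and on a two-proportion model, whereas the analysis models repeat episodes over person-weeks among all household members.

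**Conclusion.** The point holds for heat illness and for hospital visits. As written, detection of these outcomes depends on arm, through people who also deliver the intervention, and the analysis as described does not separate that from the effect of the bundle. Shared weekly visits, a common tool, de-duplication and blinded analysis reduce or leave untouched the difference; none removes it.

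The conclusion rests on reading the CG sections as they stand and on the article describing no matching control-arm channel. The size cannot be derived from the documents and the direction is not certain. The illustration shows only that a modest assumed excess, 10%, would matter: about 83% power becomes 59%. Mortality is affected by inference at most, and the sample size calculation is unaffected.

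**What to change.** 1. Reconcile Community education and awareness, Training, Control arm and Table 3: state who conducts community surveillance in each arm.
2. Define the heat-illness and hospital-visit numerators as events recorded at the scheduled weekly data-collector visits, with the same fixed recall questions in both arms, plus facility-record ascertainment run identically in both arms and not prompted by CG reports or logbooks.
3. Record the source of each event. Report CG-triggered events only in a sensitivity analysis. Do not admit a CG-flagged event merely because it is repeated at the next weekly visit, since the triggered visit itself prompts recall.
4. State that data collectors do not distribute education material at visits where outcomes are recorded.

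The cost is protocol wording, a source field, and facility-record work that no longer relies on CG leads. The sample size stays as planned. Some true events found only through CGs leave the primary count. If they are few, little is lost; if they are many, the loss is larger, but so is the bias avoided. Some recall prompted by ordinary CG contact may remain in the intervention arm, and the report should say so.

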#### Structural modification

This component will include modifications to existing structures (retrofitting) and community spaces. The specific structural intervention considered for each household within a cluster and the communal intervention will be selected from the most feasible interventions identified in the formative phase (figure 3). The household-level interventions are targeted to reduce indoor temperature, and the community interventions will play a role in reducing the effects of high heat for outdoor workers and the community. The selected interventions based on the extensive formative work are divided into three categories: heat protection, heat modulation and heat dissipation.^34^ Intervention for each selected household/structure and community space within the intervention cluster will be evaluated through a series of steps including building materials used, strength, efficiency, overshadowing, ventilation conditions and consent of residents, and after assessment of structural safety and resident safety by experts including architects and structural engineers, intervention for each dwelling would be finalised and delivered (figure 4). We will make every effort to ensure that each individual intervention is delivered proportionately in each cluster, that is, an equal number of each intervention type in every cluster.

**Figure 3 F3:**
[figure not shown]
Building survey and intervention process.

**Figure 4 F4:**
[figure not shown]
Classification of Heat Illness Symptoms.

These interventions will be delivered based on a community-participatory approach; the community and the project will share the cost of intervention to improve ownership, as shown in a previous trial.^35^ The community contribution will be approximately 15–25% of the total cost; this contribution can be monetary or non-monetary (labour). This approach would enhance the acceptability and sustainability of the interventions.

##### Information, education and communication materials

Findings from the formative phase will guide the development of educational materials. We will develop the following materials.

Posters.Pictorial brochures/flip charts.Short video messages in the local languages (Sindhi, Pashto and Urdu).

IEC materials will be distributed during CG meetings and during follow-ups through data collectors, and short videos will be shared through WhatsApp groups with disappearing message settings turned on (messages that disappear after a single view) to prevent videos from passing on and possibly resulting in control group contamination.

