### Household data collection

Baseline, monthly/weekly follow-up and end line surveys will be conducted in 22 randomised intervention and control clusters. Baseline and endline surveys will be done to collect information on various variables, including demographics (household size, socioeconomic status, education, occupation, ethnicity), healthcare seeking, mental health using the WHO wellness survey, food security, dietary diversity, co-morbidities, medications, signs and symptoms of heat-related illness (box 1). The questionnaire was developed using standardised questionnaires used during similar surveys, and some questions were modified to better accommodate local contexts. The tool was then translated into the local language and back-translated to English to validate the translation.

Box 1Section for data collection toolDescription of modules and their sectionsModule-A: Household Identification and Demographic InformationSection-A1: Household Identification and ConsentSection-A2: Household Members’ InformationSection-A3: Socioeconomic Status of Household (SES)Section-A4: Building SurveySection-A5: Household Water and Sanitation StatusModule-B: Household Food Insecurity, Dietary Diversity and Source AssessmentSection-B1: Household Food Insecurity Experience ScaleSection-B2: Household Dietary Diversity and Source AssessmentModule-C: Health and Hygiene Assessment of Adult ParticipantsSection-C1: General Health and DisabilitiesSection-C2: Mental HealthSection-C3: Hygiene Practices (Hand Washing, Dental Hygiene, Bath, (Menstrual Hygiene for Female)Module-D: Heat Exposure/Sleep/Dietary AssessmentSection D1: Work and Sun ExposureSection D2: At-home heat exposureSection D3: Heat Stress Experiences, Food Security and Adaptation StrategiesSection D4: Knowledge About Heat-Related Health Problems, Existing Heat Adaptation and Prevention StrategiesSection-D5: SleepSection-D6: Quality of life

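### The data-collector role records heat-illness symptoms and also hands out educational material in intervention clusters only, an avoidable risk of differential reporting

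*Protocol article*

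**What the plan says.** Five statements in the protocol article bear on this point.

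- **Delivery.** Information, education and communication materials: "IEC materials will be distributed during CG meetings and during follow-ups through data collectors".
- **Assessment.** Household data collection: "Data collectors will conduct weekly household visits to collect symptom data". The same section adds: "Events identified through community surveillance will trigger a household visit by data collectors who will use the same survey tool".
- **Both arms are followed up.** Household data collection: "Baseline, monthly/weekly follow-up and end line surveys will be conducted in 22 randomised intervention and control clusters".
- **Education belongs to the randomised intervention.** Intervention arm: "The ReHAB consists of two components: community education and awareness and participatory structural modifications". Control arm: "The control arm of the study will not receive any intervention other than routine care and information available through existing government response systems".
- **Another delivery route already exists.** Community education and awareness: "CGs will also distribute the relevant information, education and communication (IEC) material".

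The strengths and limitations box and Study design disclose that participants, researchers and field teams cannot be blinded, and Study design says the analysis will be blinded. Neither mentions that data collectors deliver part of the intervention.

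**The concern.** Heat-related illness, as defined in Table 1, includes conditions such as heat fatigue, heat cramps and heat rash, which will largely be known from what respondents report. The only outside check described is verification of facility visits against records where feasible, so symptoms that lead to no facility visit go unchecked.

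If the role that asks about symptoms also brings the programme's advice, answers may shift in that arm. Respondents may report fewer symptoms out of courtesy or to show that the advice works. They may also report more, because the material has made symptoms salient. Either shift would be confined to the intervention arm and would be carried into the incidence rate ratio. It could not be repaired after data collection.

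The fixed-sequence procedure under Sample size raises the stakes. Quality of life is tested only if heat-related illness is significant, so a distorted first test could wrongly open or close the second.

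**Working it through.** **Setting the statements side by side**

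1. The material is handed out by data collectors at follow-ups.
2. Symptoms are recorded by data collectors at weekly visits and at visits triggered by surveillance.
3. Follow-up takes place in both arms, but education is a component of the bundle and control clusters receive no intervention. The hand-out can therefore properly occur in intervention clusters only. This is an inference from the Intervention arm and Control arm sections; the sentence on IEC material does not itself name an arm.
4. No section describes a separate outcome assessor or a separate distributor for these hand-outs.

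The role overlap follows from the text as written.

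**Why the planned analysis does not help.** Blinding the analyst acts after the data are recorded. Intention-to-treat fixes which arm a person is counted in, not how symptoms were elicited. A cluster random intercept absorbs variation between clusters within an arm; a shift common to all intervention clusters is indistinguishable from the treatment effect.

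**The plan's own figure.** Inputs from Sample size: control prevalence 0.289, 30% relative reduction, ICC 0.0122, 80% power, two-sided 5%, 11 clusters per arm, 10% attrition.

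- Intervention prevalence: 0.289 × 0.70 = 0.2023.
- Individually randomised size: 386 per arm (409 with continuity correction).
- Households per cluster, m = n(1 − ICC)/(k − n × ICC) = 386 × 0.9878/(11 − 386 × 0.0122) = 60.6; divided by 0.9 for attrition, 67.3.
- With the continuity correction: 67.2, then 74.7.

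This agrees with the stated 70–80 households. No figure in the plan is disputed.

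**Illustration of sensitivity.** The article gives no size for a reporting shift, so the shifts below are assumptions. Take 75 households less 10% attrition, m = 67.5, and one person per household.

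- Design effect: 1 + 66.5 × 0.0122 = 1.811.
- Effective size per arm: 11 × 67.5/1.811 = about 410.
- Power = Φ{[|p1 − p2|√n − 1.96√(2p̄(1 − p̄))]/√(p1(1 − p1) + p2(1 − p2))}, with p1 = 0.289, p2 the prevalence as reported in the intervention arm, and p̄ their mean.

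| True effect | Assumed reporting shift, intervention arm | Apparent ratio | Probability of a significant result favouring the bundle |
|---|---|---|---|
| None | none | 1.00 | 0.025 |
| None | 5% lower | 0.95 | 0.07 |
| None | 10% lower | 0.90 | 0.15 |
| None | 20% lower | 0.80 | 0.47 |
| Ratio 0.70 | none | 0.70 | 0.82 |
| Ratio 0.70 | 10% higher | 0.77 | 0.59 |
| Ratio 0.70 | 20% higher | 0.84 | 0.32 |

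The table compares two proportions, as the sample-size calculation does. The planned analysis is a rate ratio over person-weeks, so the values show sensitivity and do not predict the trial's result.

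**The case against.** The strongest reply is that the added harm over what is already disclosed has not been shown. Field teams are openly unblinded. Intervention households will have visible structural changes, fortnightly summer meetings, weekly videos and weekly alerts. Courtesy reporting and heightened awareness can arise from these whoever hands over a brochure. This stands in part: the change proposed here would not remove those sources, and the increment due to the hand-out cannot be isolated. But infeasible blinding explains why assessors may know the allocation. It does not require them to deliver the intervention.

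It can also be said that a common survey tool already standardises assessment. That fixes the questions. It leaves open what else the interviewer brings or says.

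Several stronger readings are tempting, and the article does not support them:

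- **That the interviewer teaches.** The text says only that material is distributed. Sessions, outreach and demonstrations are given to the CGs, with the study team assisting at demonstrations, and the Data collection section mentions no health-message training for data collectors.
- **That hand-out and symptom interview happen at the same visit, or by the same individual.** Follow-ups are not specified, and both monthly and weekly ones exist. Only the role is shared.
- **That the weekly visit is the main source of events.** The article describes several sources and ranks none.
- **That quality of life is collected by the same staff.** The article does not say who administers WHOQOL-BREF.
- **That printed material will reach control households.** This depends on how staff are allocated to clusters, which a condensed article may leave to a field manual.

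**Conclusion.** The point holds at the level of roles. As written, the role that assesses the first-tested primary outcome also delivers part of the intervention, in intervention clusters only, and nothing separates the tasks. This is an avoidable risk of differential reporting beyond the disclosed lack of blinding.

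A reader might infer that the result will be biased in favour of the bundle. The documents do not support that: the direction could be either way and the size is not bounded. The tabulated probabilities rest entirely on assumed shifts and show only that a modest shift could matter. The conclusion also assumes that the article's single term for data collectors means one staff role; if separate teams are intended, the article should say so.

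This should be fixed because the remedy is cheap and the damage could not be undone later. It does not invalidate the design, and the sample size reproduces.

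**What to change.** - In the section on IEC materials, delete the part of the sentence that has data collectors distribute material at follow-ups.
- State that IEC material is distributed only at CG meetings, through CG outreach, and by intervention staff who collect no outcome data.
- State that data collectors neither carry nor discuss intervention material, and that they use the same scripted symptom interview in both arms.

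The cost is a short protocol edit and matching field-manual text, fewer contacts at which print is handed out, and somewhat more work for the CG volunteers. With 6–8 members per cluster of 70–80 households, each would cover roughly 9 (70/8) to 13 (80/6) households.

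This does not resolve a separate overlap: Community education and awareness also makes the CGs responsible for surveillance of heat illness. Moving the hand-outs to them leaves that issue where it is, and it needs its own answer.
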